## Abstract

**Background:** Functional dyspepsia (FD) is a common functional gastrointestinal disorder characterized by chronic digestive symptoms without identifiable structural abnormalities. FD affects approximately 8–46% of the population, leading to significant socioeconomic burdens due to reduced quality of life and productivity. Traditional medicine utilizes differential diagnosis through comprehensive examinations, which include observing and questioning, abdominal examination, and pulse diagnosis for functional gastrointestinal disorders. However, challenges persist in the standardization and objectivity of diagnostic protocols. **Methods:** This study aims to develop an artificial intelligence-based algorithm to predict identified patterns in patients with functional dyspepsia by integrating brain–body bio-signals, including brain activity measured by functional near-infrared spectroscopy, pulse wave, skin conductance response, and electrocardiography. We will conduct an observational cross-sectional study comprising 100 patients diagnosed according to the Rome IV criteria, collecting bio-signal data alongside differential diagnoses performed by licensed Korean medicine doctors. The study protocol was reviewed and approved by the Institutional Review Board of Kyung Hee University Hospital at Gangdong on 25 January 2024 (IRB no. KHNMCOH 2023-12-003-003) and was registered in the Korean Clinical Trial Registry (KCT0009275). **Results:** By creating AI algorithms based on bio-signals and integrating them into clinical practice, the objectivity and reliability of traditional diagnostics are expected to be enhanced. **Conclusions:** The integration of bio-signal analysis into the diagnostic process for patients with FD will improve clinical practices and support the broader acceptance of traditional-medicine diagnostic processes in healthcare.

## 1. Introduction

Diagnosis and prognosis are critical parts of the medical process, with treatment and follow-up management strategies based on the diagnosis of a disease. In traditional medicine, such as traditional Chinese and Korean medicine, instead of identifying the disease itself, a pattern of symptoms is identified based on overall health conditions, including disease-related symptoms (e.g., gastrointestinal symptoms) and other lifestyle factors (e.g., working hours, sleep patterns, constitution, etc.) and subjective experiences that may not be detected by diagnostic medical devices (e.g., endoscopy, blood tests). This approach is known as the pattern identification method [1]. Based on the identified pattern, Korean medicine doctors prescribe herbal medicine, acupuncture, and manual therapies such as Chuna. Generally, Korean medicine is used primarily for musculoskeletal disorders, functional gastrointestinal disorders, and psychological conditions. In Korean medicine, functional dyspepsia (FD) is diagnosed using a technique involving four phases of examination: interview and observation, listening and smelling, questioning, and palpation. However, key diagnostic methods such as tongue diagnosis, pulse diagnosis, and abdominal diagnosis remain subjective and lack standardization. Recent advancements have included the development of standardized questionnaires to facilitate quantitative assessments for patterns, such as spleen and stomach deficiency–cold pattern, spleen and stomach damp–heat pattern, and food stagnation pattern in patients with FD [2]; However, diagnostic protocols used in clinics still heavily rely on these four examinations. Pulse diagnosis is a cornerstone in traditional medicine for determining conditions such as deficiency–excess (deficient or excessive energy level) and cold–heat patterns. For this examination, doctors continue to rely on their tactile perception, and various medical subdisciplines propose different methods for palpation and interpretation of these subjective sensations, leading to variability and challenges in objective assessments [3,4]. FD poses a significant challenge in healthcare due to its chronic nature and the lack of standardized, objective diagnostic tools. The diagnostic process remains largely reliant on the practitioner’s expertise and interpretation, leading to variability in diagnosis and treatment outcomes. Additionally, there is a critical gap in integrating objective, quantifiable data into the diagnostic process to enhance accuracy and consistency in the diagnosis of FD. Thus, a new approach is needed to address this gap by developing more comprehensive and data-driven diagnostic models.

Pulse wave signals, generated by radial artery pulsations, reflect hemodynamic changes. Technological advancements have led to the development of pulse diagnostic devices that analyze variables, such as power spectrum, signal amplitude, frequency, regularity, and volume. In particular, the measurement of pulse signals and the analysis of pulse wave signals are increasingly used for the diagnosis and monitoring of cardiovascular and systemic diseases like diabetes, thereby expanding their clinical applications. Recent studies have explored artificial intelligence (AI) techniques to analyze pulse wave time-series data, aiming to extract clinically meaningful information and provide objective interpretations of traditional pulse patterns with significant prediction accuracy [5,6,7,8].

Functional dyspepsia (FD) is a relapsing and remitting chronic gastrointestinal disorder characterized by postprandial fullness, early satiation, and epigastric pain or burning not associated with defecation, which are not fully explained by other medical conditions [9]. Patients with FD exhibit altered brain activity in regions including the prefrontal cortex, somatosensory cortex, insula, anterior cingulate cortex, amygdala, and hippocampus [10,11,12]. Additionally, autonomic nervous system activity is an important diagnostic factor in gastrointestinal disorders, as imbalanced sympatho-vagal and autonomic responses are associated with alterations in gastrointestinal functions and symptoms [13]. For example, patients with FD showed a significantly increased skin conductance response (SCR) in response to external stressful stimuli compared to healthy controls [14], and patients diagnosed with both postprandial distress syndrome and epigastric pain syndrome showed a significantly greater low frequency/high frequency ratio measured by heart rate variability (HRV) after a drink test [15].

Although the single measurement of bio-signals (e.g., ECG, SCR, pulse, and functional near-infrared spectroscopy [fNIRS]) has contributed to the scientific understanding of the underlying pathophysiological status of FD, integrating multiple bio-signals may provide a more comprehensive understanding of FD and enhance the objectivity of diagnostic outcomes. This is because brain–body interactions and patterns in multivariate data may reveal crucial patterns useful for the diagnosis of FD. For example, the integration of brain–body bio-signals (multimodal measurements of neuroimaging data and autonomic metrics) with AI algorithms has shown the potential to address the subjectivity of pain reports [16,17], which may lead to the development of precision pain treatments [18]. However, until now, such an approach has not been attempted for pattern differentiation diagnosis of FD. A few studies have employed machine learning techniques to predict treatment responses [19,20] and identify key clinical symptoms in FD [21]. However, no studies have developed AI models using bio-signal data for pattern identification of FD. Since the diagnosis of FD is primarily conducted subjectively, this approach is not only novel but also clinically valuable. By leveraging advanced AI techniques to analyze these bio-signals, our research bridges the gap between traditional diagnostic practices and modern technological advancements, providing a more comprehensive understanding of patient conditions and potentially improving treatment outcomes.

We hypothesize that incorporating objective bio-signal data obtained from the brain and the body will enhance the predictive accuracy of differential diagnoses in patients with FD. This study aims to bridge the gap by developing an AI-based algorithm that integrates brain–body bio-signals to predict pattern differentiation outcomes, potentially contributing to the standardization and objectification of diagnostic methods in Korean medicine. To achieve this goal, we will conduct a cross-sectional clinical trial with 100 patients diagnosed with FD by ROME IV criteria, measuring brain activities, autonomic metrics, and pulse signals.

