For time-series bio-signals, various machine learning techniques have been shown to be effective in identifying spatiotemporal patterns for predictive and diagnostic tasks [39]. For single-channel signals, such as ECG or SCR, we plan to extract meaningful features that represent the physiological state or detect abnormalities using machine learning models, such as the random forest model. These features include traditional metrics (e.g., R-peak detection and morphological analysis) as well as advanced decomposition techniques (e.g., wavelet transforms and empirical mode decomposition) that facilitate the extraction of time–frequency domain characteristics to capture subtle and non-stationary signal behaviors [40]. Furthermore, deep learning-based methods, including 1D convolutional neural networks (CNNs) and transformer architectures, will be employed for automated and robust representation learning directly from raw signals.

For multi-channel signals, such as fNIRS or pulse wave data, we will utilize both linear and non-linear analytical methods to evaluate signal rhythms and variability. Recently introduced approaches (e.g., network analysis and attention-based models) allow for the modeling of long-term dependencies, revealing spatiotemporal patterns that traditional methods often fail to detect [41,42]. Graph-based models, such as graph neural networks and graph convolutional networks, show potential for analyzing inter-channel connectivity and exploring the functional relationships among multiple bio-signal sources [43]. By leveraging classical connectivity metrics, such as phase-locking values or mutual information, we expect these integrated approaches to yield more accurate and interpretable results.

To address potential confounding variables, we have identified key confounders such as variability in bio-signal measurements, subjectivity in diagnoses, and multi-collinearity among bio-signals. We will use multivariate regression and regularization techniques like Least Absolute Shrinkage and Selection Operator or ridge regression to handle multi-collinearity and apply principal component analysis for dimensionality reduction. Additionally, to ensure our models are based mainly on bio-signals, we will exclude questionnaire scores that strongly correlate with specific patterns. This approach helps maintain model robustness and aligns with our primary study objective.

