Additionally, we will investigate local and relative differences in brain activity through amplitude and frequency power analysis. Frequency-domain techniques (e.g., Fast Fourier Transform (FFT), Short Time Fourier Transform (STFT), and wavelet transforms) can be applied to extract spectral features from bio-signals, capturing power distributions across key frequency bands [44]. Recent hybrid approaches transform time-frequency representations into image-like inputs, enabling the use of CNN-based models to automatically discern frequency-related patterns. These methods can be used to enhance the sensitivity of diagnostic tools, particularly for complex and non-stationary bio-signals [45]. The significance and validity of the model will be assessed based on the classification accuracy and the area under the receiver operating characteristic (ROC) curve. These metrics will be obtained through bootstrapping and cross-validation methods and tested against a chance level (0.5, 0.33, or 0.17, depending on the prediction outcomes) using a *t*-test with a significance level of *p* < 0.05.

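### The hypothesis is that bio-signals improve predictive accuracy, but section 2.8 tests the models only against chance and names no reference model

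*Protocol article*

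**What the plan says.** The Introduction (section 1) states: "We hypothesize that incorporating objective bio-signal data obtained from the brain and the body will enhance the predictive accuracy of differential diagnoses". The same section argues that integrating several bio-signals may give a fuller and more objective picture than single measurements.

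Section 2.8 fixes how the models are judged. Performance is "assessed based on the classification accuracy and the area under the receiver operating characteristic (ROC) curve", obtained by bootstrapping and cross-validation, and "tested against a chance level (0.5, 0.33, or 0.17, depending on the prediction outcomes"), with a t-test at the 5% level.

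Section 2.8 also has a paragraph on confounding: "we have identified key confounders such as variability in bio-signal measurements, subjectivity in diagnoses, and multi-collinearity among bio-signals". The remedy follows: "We will use multivariate regression and regularization techniques like Least Absolute Shrinkage and Selection Operator or ridge regression to handle multi-collinearity", with principal component analysis for dimension reduction. Questionnaire scores that correlate strongly with a pattern are left out, so that the models rest mainly on bio-signals.

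Section 2.6 collects demographic data, height, weight, medication, a symptom VAS and, for women, menstrual cycle details. Section 2.8 gives none of these a named role in judging the models.

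**The concern.** To say that adding something improves accuracy, one needs the accuracy without it. The hypothesis needs a model without bio-signals as comparator. The argument for integration needs a single-modality model. The planned null is chance, which is neither.

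Heart rate variability, pulse wave and skin conductance may vary with age, sex and body size, and so may the doctor's pattern label. If so, a bio-signal model can beat chance by recovering what a short demographic form already gives. Under the plan as written, that result could be reported as support for the hypothesis, although the hypothesis had not been tested.

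The confounder paragraph does not close the gap. Variability in the signals is predictor noise, subjectivity in diagnosis is error in the label, and multi-collinearity is correlation among predictors. None of them is a variable shared by signal and label. Shrinkage and principal components stabilise a fit; they do not separate bio-signal information from demographic information.

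**Working it through.** **1. The plan's own figures.** Section 2.3 asks for 50 patients per category and recruits 100. Since 50 × 2 = 100, 50 × 3 = 150 and 50 × 6 = 300, the sample size fits a two-class outcome. The chance levels in section 2.8 are 1/k: 1/2 = 0.50, 1/3 = 0.33, 1/6 = 0.17. Both reproduce. Neither involves a comparison between models.

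**2. What passes the test, by AUC.** Inputs: n = 100 (section 2.3); two classes of 50 (assumed).

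- Mann-Whitney null SE = √[(n₁ + n₂ + 1)/(12 n₁ n₂)] = √[101/(12 × 50 × 50)] = √(101/30000) = 0.058.
- Two-sided 5% limit: 0.5 + 1.96 × 0.058 = 0.614.
- AUC of 0.60, 0.65 and 0.70 (assumed range) gives z = (AUC − 0.5)/0.058 = 1.72, 2.59 and 3.45.

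This is the standard error for a rank test, used as a yardstick. It is not the planned t-test on resampled metrics.

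**3. What passes, by accuracy.** With chance 0.5 and n = 100, an exact one-sided binomial test rejects at 59 or more correct (α = 0.044). A classifier with true accuracy 0.60, 0.65 or 0.70 rejects with probability 0.62, 0.91 or 0.99, whatever the source of that accuracy.

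**4. Imperfect proxies.** Step 2 does not say how often a proxy would reach such an AUC, so this was simulated: 400 runs per setting, n = 100, binary pattern depending only on age and sex, and five bio-signals that carry age/sex information plus noise and nothing else. All effect sizes are assumptions. β is the log-odds per SD of age and per unit of sex coded −1/+1. ρ is the correlation of each signal with the age/sex score.

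| β | ρ = 0.3 | ρ = 0.5 | ρ = 0.7 |
|---|---|---|---|
| 0.4 | 11% | 24% | 30% |
| 0.7 | 23% | 57% | 75% |
| 1.0 | 43% | 80% | 93% |

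Entries are the share of runs in which a t-test on ten fold accuracies rejects 0.5. At β = 0 it rejects in about 5%. A likelihood-ratio test of the bio-signals added to age and sex rejects in about 5–8% of runs in the nine settings of the table, near its nominal 5%. The test against chance responds to demographic information; the nested test does not.

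**5. Precision of the increment.** A second simulation took n = 100, three baseline predictors, five informative bio-signals, ridge logistic regression, ten folds and a paired patient-level bootstrap interval (200 runs each, effects assumed). It detected a gain in AUC from 0.65 to 0.71 in 19% of runs, from 0.64 to 0.74 in 36%, and from 0.63 to 0.78 in 73%.

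**The case against.** The best defence is that the Abstract and Introduction give the aim as developing an algorithm that predicts the pattern from bio-signals, and the Discussion calls the study an initial step. For a first development study, a test against chance answers that aim, and the mismatch comes down to one verb in the hypothesis. This stands in part: rewording the hypothesis is a legitimate repair. But the hypothesis as printed is incremental, and the article itself fixes chance as the null, so the matter is not simply left open for an analysis plan.

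Safeguards do exist. Section 2.4.2 excludes drugs that could influence the signals on the measurement day, and excludes cardiac disease. Section 2.8 drops questionnaire scores strongly tied to a pattern, and also plans group comparisons, correlations, and mediation and moderation analyses. These narrow the concern. None of them estimates a gain in predictive accuracy.

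Three stronger readings are tempting, and the documents do not support them.

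- *The models would be biased by confounding.* The aim is prediction, not a causal effect. A predictor that works partly through age is not biased; it has less added value. The confounder list is also introduced as examples, so it is not exhaustive.
- *Proxy signals would beat chance.* They could. No section says that demographics predict the pattern, and with weak effects the simulated rejection rate is 11–30%.
- *The study cannot answer its question.* That is true only of the analysis as written. The data for the comparison are being collected.

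**Conclusion.** The point holds as a mismatch between hypothesis and test. A significant result under section 2.8 would show that the model predicts better than chance. It would not show that bio-signals improve accuracy, or that combining them beats the best single one.

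With two equal classes and 100 patients, any AUC above about 0.61 passes by the Mann-Whitney yardstick. Signals that are pure age/sex proxies passed a fold-based t-test in 11% to 93% of simulated runs. That range rests entirely on assumed effect sizes and shows what is possible, not what will happen in this study.

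The confounder paragraph should be corrected because it lists the wrong kind of variable and offers methods that do not deal with shared demographic information. It does not by itself make the models invalid.

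**What to change.** In section 2.8, on identical patient-level folds, fit:

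- (A) a reference model of age, sex and BMI;
- (B) A plus the bio-signals;
- (C) each modality alone.

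Report the paired difference in cross-validated AUC, B minus A, and multimodal minus best single modality, each with a patient-level bootstrap confidence interval. Base any statement that bio-signals improve accuracy on B minus A. If only the test against chance is kept, reword the hypothesis in section 1 as prediction better than chance.

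Add current medication and symptom VAS to A as a sensitivity analysis, with menstrual phase in women only, since it is recorded only for them. VAS does not belong in the main reference model: symptoms are part of what the pattern label rests on, so requiring a gain beyond VAS is a stricter question than the one asked. Its timing also needs reconciling, because Table 1 lists VAS at Visit 1 only, while the Discussion places it at the time of bio-signal measurement.

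Describe LASSO, ridge and PCA as handling of collinearity and dimension, not of confounding.

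The cost is wording and extra model fits on data already being collected. The real downside is precision: at 100 patients the increment may well be inconclusive (working, step 5). Making B minus A the sole decisive test is therefore debatable. Reporting it with its interval is the minimum needed to support the claim.

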## 2. Methods

### 2.1. Study Design and Setting

This is an observational cross-sectional study combined with the development of an AI model. It will be conducted at Kyung Hee University Hospital in Gangdong, South Korea. Table 1 provides a summary of the study flowchart.

### 2.2. Ethical Considerations

The study protocol was reviewed and approved by the Institutional Review Board of Kyung Hee University Hospital at Gangdong on 25 January 2024 (IRB no. KHNMCOH 2023-12-003-003). This study was registered in the Korean Clinical Trial Registry, named Clinical Research Information Service (CRIS, registration no. KCT0009275). All information regarding the study protocol will be provided to each participant. Written informed consent will also be obtained. The study will adhere to the Declaration of Helsinki and Good Clinical Practice guidelines. Participants have the right to withdraw from the study at any time. If a participant withdraws consent or does not comply with study procedures, their participation may be terminated. Participants will also be withdrawn if they are found to violate inclusion criteria or if any adverse events or comorbidities occur that make continued participation inappropriate.

### 2.3. Sample Size Calculation

Based on machine learning model requirements for predictive validity with categorical variables, a minimum of 50 samples per category is deemed necessary [22,23,24,25]. Considering potential variability and ensuring sufficient data for model training and validation, we aim to recruit 100 patients with FD.

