The second visit will involve a review of medication use and menstrual cycle details for female participants. The vital signs will be measured again, and participants will complete a series of questionnaires, including the Standard Tool for Pattern Identification of FD [2], Cold–Heat Pattern Questionnaire [26], Deficiency–Excess Pattern Questionnaire [27,28], Phlegm Pattern Questionnaire [29], Food Retention Questionnaire [30], Spleen Qi Deficiency Questionnaire [31,32], Stomach Qi Deficiency Questionnaire [33], Nepean Dyspepsia Index (NDI) [34], State-Trait Anxiety Inventory (STAI) [35], Beck Depression Inventory-II (BDI-II) [36], and the EeroQol-5-Dimension (EQ-5D) [37]. Participants may opt out of answering any questions they find uncomfortable. The Standard Tool for Pattern Identification of FD questionnaire comprises 45 items that categorize FD symptoms into six types: liver–stomach disharmony, dampness and heat in the spleen and stomach, spleen and stomach deficiency and cold, tangled cold and heat, food retention disorder, and insufficiency of stomach yin. This questionnaire demonstrates high reliability, indicated by its internal consistency, and a moderate level of validity, based on correlation analyses between the FD patterns identified by the tool, the Rome IV subtypes, and other dyspepsia-related questionnaires [2]. In addition, the Cold–Heat Pattern Questionnaire [26], Deficiency–Excess Pattern Questionnaire [27,28], Phlegm Pattern Questionnaire [29], Food Retention Questionnaire [30], Spleen Qi Deficiency Questionnaire [31,32], and Stomach Qi Deficiency Questionnaire [33] have been developed as pattern identification tools. These patterns are recognized as being significantly related to FD and the tools have been validated for both reliability and validity.

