### 2.7. Data Collection

Pattern identification will be conducted by licensed Korean medicine doctors via questioning, tongue diagnosis, pulse diagnosis, and abdominal diagnosis. This assessment determines deficiency–excess, cold–heat, and the presence of phlegm or food stagnation, as well as six primary FD differentiation patterns (spleen and stomach deficiency–cold, spleen Qi deficiency, liver–stomach disharmony, food stagnation, spleen deficiency with damp–heat, mixed cold and heat).

Bio-signal measurements will be conducted during the second visit or during the first visit only if the screening procedures confirm that the participants meet the inclusion criteria. Prefrontal cortex activity will be measured using a headband-type fNIRS device (NIRSIT; OBELAB Inc., Seoul, Republic of Korea). SCR, ECG, and pulse wave signals will be recorded with electrodes attached to the fingers, wrist, and chest, connected to the Biopac MP160 system (BIOPAC Systems Inc., Goleta, CA, USA). Radial artery pulse waves will also be measured using the DMP-LIFE PLUS pulse analyzer (DAEYOMEDI Co., Ltd., Ansan, Republic of Korea). These measurements will be conducted with the participants in supine position for two minutes. To maintain objectivity, the researcher measuring biometric signals will be different from the doctors diagnosing the patients with FD. Additionally, the diagnosis and pattern identification results will be blinded to both the researcher and the participants. Throughout the measurements, participants will be monitored thoroughly for any discomfort or adverse events.

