### 2.8. Statistical Analysis

Categorical variables include pattern identification results diagnosed by the Korean medicine doctors and those obtained from questionnaires for pattern identification. These variables will be used for subgroup analyses and as outcomes for AI-based prediction models, facilitating comparisons of differentiation patterns based on specific diagnostic results and bio-signals.

The questionnaire results of the NDI, STAI, BDI-II, and EQ-5D will be treated as numerical variables. The normality of the questionnaire results will be assessed to determine suitable statistical tests. Depending on normality, statistical tests like *t*-tests, analysis of variance, or non-parametric tests will be used to compare groups. Subgroup analyses will compare bio-signals between different diagnostic patterns. Correlation analyses will explore the relationships between the questionnaire results and categorical variables, while mediation and moderation analyses will assess potential factors that mediate or moderate the effects among the variables.

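### The total of 100 meets the protocol's own minimum of 50 per category only for a near-even two-category outcome; the six-category and implied three-category predictions would need at least 300 and 150

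*Protocol article*

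**What the plan says.** Section 2.3 (Sample Size Calculation) gives one rule, tied to predictive validity for categorical variables: "a minimum of 50 samples per category is deemed necessary". After a general reference to variability and to data for training and validation, it concludes: "we aim to recruit 100 patients with FD". The article gives no other basis for the number.

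The outcomes to be predicted are described elsewhere:

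- Section 2.8 (Statistical Analysis) covers pattern results from both the doctors and the questionnaires: "These variables will be used for subgroup analyses and as outcomes for AI-based prediction models".
- Section 2.7 (Data Collection) has the doctors assess deficiency–excess, cold–heat and the presence of phlegm or food stagnation, "as well as six primary FD differentiation patterns".
- Section 2.6 (Study Procedures) describes the standard pattern tool, which "comprises 45 items that categorize FD symptoms into six types".
- Section 2.8 says model performance will be "tested against a chance level (0.5, 0.33, or 0.17, depending on the prediction outcomes", at a 0.05 significance level.

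**The concern.** A chance level of 0.17 is one in six and 0.33 is one in three, so the plan intends to fit and significance-test models with more than two classes. Section 2.3 states its minimum per category without limiting it to two-category outcomes, yet the total fits only two categories.

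Nothing in the article merges patterns, sets recruitment quotas by pattern or exempts the multi-class models from the rule. A reader of Section 2.3 would therefore take the six-pattern model to be adequately sized by the authors' own standard, which it is not. Performance in the rarer patterns would rest on few patients, and a multi-class result could be presented as having a validity that the sample size was said to secure.

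**Working it through.** **Inputs, all from the protocol article**

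- Minimum per category, m = 50 (Section 2.3)
- Planned total, N = 100 (Section 2.3)
- Number of categories, k = 2, 3 or 6, read from the chance levels 0.5, 0.33 and 0.17 (Section 2.8). k = 6 is also explicit in Sections 2.6 and 2.7. k = 3 is an inference, because no three-level outcome is named.

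**Step 1: reproduce the planned total.** The smallest total that satisfies the rule is k x m, reached when categories are exactly equal and no patient is lost. For k = 2 this is 2 x 50 = 100, which matches. The allowance above the minimum is 100 − 100 = 0.

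**Step 2: apply the same rule to the other outcomes.**

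| Categories | Minimum total (k x 50) | Average per category at N = 100 | Share of the minimum |
|---|---|---|---|
| 2 | 100 | 50 | 100% |
| 3 | 150 | 33.3 | 67% |
| 6 | 300 | 16.7 | 33% |

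The 150 and 300 are lower bounds. The smallest category can never exceed the average, so at N = 100 it holds at most 33 patients (three categories) or 16 (six categories). Since 100 / 50 = 2, at most two of the six patterns could reach 50, and then only if the other four were empty.

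**Step 3: how little room the two-category case has.** The article gives no prevalence or loss rate, so the following values are assumptions.

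- Minority share 40%: expected count 0.40 x 100 = 40; an expected count of 50 needs 50 / 0.40 = 125 patients.
- Minority share 30%: expected count 30; an expected count of 50 needs 50 / 0.30 = 167 patients.
- Loss of 5% or 10% of patients with a perfect split: 95 / 2 = 47.5 or 90 / 2 = 45 per category.

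Step 3 shows that there is no reserve. It does not show that two-category models fail.

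**The case against.** The best defence is that this is model development and that 50 per category is a rule of thumb whose cited basis cannot be examined here. That is fair as far as it goes: the check shows that the plan contradicts itself, not that 50 is the right standard or that a useful six-pattern model is impossible with 100 patients. But the article calls the figure a necessary minimum and offers no other justification for N. It does not label the multi-class models exploratory. If the rule does not bind, the total has no stated basis.

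A second defence is that the article condenses a fuller protocol. That would excuse an absent dropout allowance. It does not reconcile a rule, a total and a set of outcomes that are all printed and cannot all hold.

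Several stronger readings are tempting but not supported:

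- *The six-pattern model is the main endpoint.* In "six primary FD differentiation patterns" the adjective describes the patterns. No prediction target is ranked first.
- *Two-category outcomes nearly always miss the minimum.* With a true 50% share, an exact 50:50 split has probability of only 0.08, but this counts 49:51 as failure. Under the same assumption both categories reach at least 45 with probability 73% and at least 40 with probability 96%.
- *Signal rejection shrinks the sample further.* The fNIRS and pulse-wave cleaning in Section 2.8 works on channels and sensors. Nothing says that the patient is dropped. Withdrawals are possible under Section 2.2, but no rate is given.
- *Deficiency–excess or cold–heat is a safe two-category target.* The article does not state how many levels they have, and either could be the source of the 0.33 chance level.

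**Conclusion.** The point holds as an internal contradiction in the stated basis for the sample size. The total of 100 is consistent with the 50-per-category rule for two-category outcomes only, approximately and without reserve. For the six-category patterns it gives a third of the stated minimum (about 17 against 50; 100 against at least 300 in total). For the implied three-category outcome it gives two thirds (about 33 against 50; 100 against at least 150).

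The conclusion assumes that a category in Section 2.3 means an outcome class, and that the chance levels are one divided by the number of classes. The three-category part rests on the 0.33 alone. The six-category part does not depend on that inference or on any assumption about prevalence or losses.

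**What to change.** Keep 100 patients and change the wording.

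1. In Section 2.3, say that 100 meets the 50-per-category minimum only approximately, only for two-category outcomes with a near-even split, and with no reserve for imbalance or withdrawals.
2. In Section 2.8, label the three- and six-category models as exploratory and below the stated minimum. Name the outcome to which the 0.33 level belongs.
3. Report those models with the number of patients in each class and with confidence intervals that reflect the cross-validation or bootstrap. A simple binomial interval that treats the 100 patients as independent test cases need not apply. Make no claim that predictive validity is ensured.

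Reconciling the sections does not require naming a single confirmatory target, although the authors may choose to do so.

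The cost is wording only, with no added enrolment or measurement. The price is a weaker claim for the multi-class models. Keeping the full claim under the present rule would mean at least 300 patients, and more if the patterns are uneven.
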